### Overview of study design

This is a randomised controlled trial to test the effect of an automated electronic feedback system on CVD prevention in general practice. The practice populations over the age of 50 years will be randomised into two groups: "intervention" and "control". Intervention patients currently belonging to one of the high risk search groups described below will have alert messages appear on the screen when their electronic notes are opened. We will also apply an electronic search protocol every eight weeks to both groups throughout the study, to produce continually updated lists of potentially high risk patients for cardiovascular events. For the intervention group the patients on these lists will be revealed to the practice. The clinical software company EMIS, who serve the majority of practices in Warwickshire and Coventry, have programmed their software to produce the alerts and the eight-weekly lists for intervention patients. This "intervention" involves the feedback to practice teams to identify patients who are currently at high estimated risk, patients whose data is incomplete (who may benefit from updated measurements of cholesterol, blood glucose, blood pressure or recording of smoking status) and those who may have undiagnosed diabetes, through the alert messages and the eight-weekly lists. The control group will receive the usual care provided under the nGMS contract. No information will be withheld from the clinicians regarding control patients, the only difference will be the absence of reminders to draw their attention to the information. The practice teams themselves will decide on any changes in treatment in consultation with individual patients in both arms of the study, allowing care to remain tailored at the clinician-patient level. Outcomes will include the number of cardiovascular events and the number of high risk patients in the two populations (defined by inclusion on the eight-weekly search results). The design of the search protocol and the justification for the thresholds are described in the appendix.

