### Randomisation

Participating practice patients over 50 years of age will be randomised into two groups – "intervention" and "control." Patients will be consistently allocated to these groups throughout the study using an electronic technique that is concealed to all researchers and practitioners involved. This process will occur electronically during each search, so that those who join the practice during the study will be randomised automatically as soon as they are first provided with electronic notes as a fully registered patient. Temporary residents are not included in the study.

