### Sample size calculation

#### Event rates

Our study defines a cardiovascular event as a new diagnosis of CVD, a new myocardial infarction, a new stroke, a new transient ischaemic attack, or sudden death from CVD. A new stroke in someone with a previous stroke will count as a new event. An acute myocardial infarction in a patient previously diagnosed with angina will be recorded as a new event, but a new onset of angina in a patient who already had a diagnosis of acute myocardial infarction might not be recorded as a new diagnosis, as the patient will already be on the CHD register.

The British Heart Foundation [35] has compiled an estimate of the number of cardiac events in the UK population in 2002 from several available data sources. The number of myocardial infarctions (all ages) was estimated to be 268,000, while the number of new cases of angina (all ages) was estimated to be 338,000

The UK population was 59,321,700 in 2002 [Sources: Office for National Statistics, General Register Office for Scotland, Northern Ireland Statistics and Research Agency], so estimated incidence rates *for coronary heart disease *are

**Incidence of myocardial infarction **451.77 per 100,000

**Incidence of new case of angina **569.77 per 100,000

For *cerebrovascular disease*, the OXVASC study [36] provides a local source of information drawn from an Oxfordshire population. The incidence rates were:

**Incidence of stroke **187 per 100,000

**Incidence of TIA **51 per 100,000

Therefore

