#### Estimating population size needed

A Poisson distribution model is appropriate for events that are rare on an individual level, occurring randomly and independently at a constant rate in a population [37].

Assuming a Poisson distribution, the formula for the sample size is:

where:

λ_0 _= the expected incidence of cardiovascular events (i.e. 1260/100,000)

δ = new incidence in the intervention group

*z*_1-*α *_= standardised normal distribution value based on 0.05 significance level

*z*_1-*β *_= standardised normal distribution values for 80% power

*N *= total number of patients required in the study

*Nw *= total number of patients required in the study + 10% to account for practice withdrawal

For 80% power and 0.05 significance level (2-tailed) [38] (see Table 1):

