**Table 1 T1:** 

Reduction in incidence (%)	*z*_1-*α*_	*z*_1-*β*_	λ_0_	δ	N	Nw
10	1.96	0.8416	0.0126	0.001260	64133.46	70546.80

The practice population required to detect both statistically and clinically significant changes in the cardiovascular event rate is therefore estimated to be approximately **70,000**, the combined list size of all age groups in participating practices.

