### 1. Justification for the thresholds and search protocols used in the study

#### a) Age group

We decided to include in the searches only those patients over 50 yrs, as the prevalence of cardiovascular disease begins to climb steeply at this age [35]. As the main outcome involves a comparison of the effect of the intervention on event rates, this will avoid the dilution of each denominator population by low risk patients.

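### The sample size section uses an all-age event rate and an all-age list, so its rate and N do not describe the over-50s who are randomised

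*Protocol article*

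**What the plan says.** **Who is in the trial.** The overview of study design says: "The practice populations over the age of 50 years will be randomised into two groups". The Randomisation section agrees: "Participating practice patients over 50 years of age will be randomised into two groups". Appendix 1a links the age limit to the event-rate comparison: "this will avoid the dilution of each denominator population by low risk patients".

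**Where the rate comes from.** Under Event rates: "The number of myocardial infarctions (all ages) was estimated to be 268,000", and "the number of new cases of angina (all ages) was estimated to be 338,000". Both counts are divided by the whole population: "The UK population was 59,321,700 in 2002". Stroke (187 per 100,000) and TIA (51 per 100,000) are added from a local Oxfordshire study. The total, 1260 per 100,000, becomes λ0.

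**What N is.** Under Estimating population size needed, N is the "total number of patients required in the study". Table 1 gives N = 64133.46, and 70546.80 after adding 10% for practice withdrawal. The sentence below Table 1 then describes the resulting 70,000 as "the combined list size of all age groups in participating practices".

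**The concern.** The two descriptions of N cannot both hold. People on the list aged 50 or under are never randomised, so an all-age list is not a number of study patients. λ0 is likewise not the rate to expect in either arm, because over-50s have events more often than the whole population does. The section states no over-50 rate, no number of over-50s and no expected events among them.

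Two things are at stake. A reader may take 70,000 as the number randomised, or 1.26 per 100 person-years as the expected control-arm rate, and both would be wrong. Also, an all-age rate applied to an all-age list counts events under 50 that cannot occur in the trial, so expected events and power are somewhat too high.

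**Working it through.** **Inputs from the protocol.** Infarctions 268,000; angina 338,000; population 59,321,700; stroke 187 and TIA 51 per 100,000; λ0 = 0.0126 per year; δ = 0.00126 (a 10% reduction); z values 1.96 and 0.8416; withdrawal allowance 10%; outcome assessed over two years and a third year.

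**Assumptions (not in the protocol).** Share of all events occurring under 50, u = 5–20%. Share of the list over 50, f = 30–40%. Allocation 1:1.

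**1. The rate.** 268,000/59,321,700 = 451.77 and 338,000/59,321,700 = 569.77 per 100,000. The sum 451.77 + 569.77 + 187 + 51 = 1259.5, which rounds to 1260. The two counts labelled as all-age supply 1021.5 of this, or 81%.

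**2. Table 1.** The formula is not legible in the text at hand. A one-sample Poisson form, testing one population against a fixed rate, reproduces the table:

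N = (1.96·√λ0 + 0.8416·√(λ0 + δ))² / δ² = 64,133.46, and 64,133.46 × 1.1 = 70,546.8.

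The two-sample form does not: (1.96 + 0.8416)² × (0.0126 + 0.01134) / 0.00126² = 118,357 per arm, or 236,715 in total. Since λ0 is an annual rate, N is in effect person-years.

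**3. What the age mismatch costs.** The over-50 rate is λ0(1 − u)/f and the number of over-50s is f × list. In the product f cancels, so annual events at the control rate are list × λ0 × (1 − u). For a list of 70,000 this is 882 when u = 0, 838 at 5%, 794 at 10% and 706 at 20%. Poisson power depends on expected events, so the cost is a factor 1/(1 − u) on the list, not 1/f.

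On the plan's formula, for one year at N = 64,133:

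power = Φ[(δ·√(N(1 − u)) − 1.96·√λ0) / √(λ0 + δ)]

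| u | Power | List needed, 64,133.46/(1 − u) |
|---|---|---|
| 0 | 80% | 64,133 |
| 5% | 78% | 67,509 |
| 10% | 76% | 71,259 |
| 15% | 74% | 75,451 |
| 20% | 71% | 80,167 |

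From u = 10% upwards, the list needed before any withdrawal already exceeds 70,547, which includes the withdrawal allowance.

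**4. The over-50 rate.** 0.0126 × 0.95/0.30 = 0.0399 and 0.0126 × 0.80/0.40 = 0.0252. That is about 2.5–4.0 per 100 person-years against the stated 1.26, in 21,000–28,000 people (30–40% of 70,000).

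**5. The two-arm comparison.** With E0 and E1 = 0.9·E0 expected events per arm, power = Φ[(E0 − E1)/√(E0 + E1) − 1.96]. For a 70,000 list over two years with u = 0, E0 = 35,000 × 0.0126 × 2 = 882 and E1 = 793.8. The ratio is 88.2/√1675.8 = 2.155, and power is Φ(0.195) = 58%.

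| u | Two years | Three years |
|---|---|---|
| 0 | 58% | 75% |
| 5% | 56% | 73% |
| 10% | 53% | 71% |
| 20% | 49% | 66% |

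The fall from 80% to 58% or 75% in the top row occurs with no age effect at all. Age takes off roughly a further 2–10 points.

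**The case against.** The strongest defence is that rate and population are matched. An all-age rate is applied to what the protocol openly calls an all-age list, the arithmetic reproduces, and expected events are nearly right. This stands, and it limits the point to a modest loss plus a wrong description.

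Three stronger readings are tempting, and the protocol does not support them:

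- *A reader might apply 0.0126 to the over-50s alone*, which would give 22–28% power at two years for f = 30–40%. That uses the wrong rate for this group: the fewer people on the list are over 50, the higher their rate must be for the same events.
- *A reader might infer that the plan's own formula fails to give 80% power in general.* The 78–71% figures hold for one year at 64,133. Over two years the same one-sample formula gives 94% even with 20% of events under 50. For one year on a full 70,000 list with no withdrawals, it stays at 80% or more up to an under-50 share of about 8.4%.
- *A reader might blame age for the whole two-arm shortfall.* Most of it comes from using a one-sample formula for a comparison of two randomised arms, and correcting the age basis alone would not recover it.

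It can also be said that sudden cardiovascular death counts as an event but has no separate term in the rate. That might offset part of the loss. The protocol does not show whether such deaths are already inside the infarction count, so the net direction is not settled. The defence leaves the conflict between the two descriptions of N unresolved.

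**Conclusion.** The point holds as a mismatch between the sample size section and the trial population. λ0 is not the over-50 rate, and N is not a number of study patients but all-age list person-years. The effect of age on power is modest: 2–9 points on the plan's own one-year calculation, if 5–20% of events occur under 50. The over-50 rate would be about two to three times the stated one, if 30–40% of the list is over 50. Both ranges are assumptions.

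The more serious overstatement of power is separate. For two arms at 1:1 on a 70,000 list, power is about 58% over two years and 75% over three before any age correction, and 56–49% and 73–66% after it. The section should be corrected. The age mismatch alone does not call for a change of design.

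**What to change.** - State λ0 as the expected event rate in patients over 50, with its source and an explicit assumption about the share of events under 50.
- State N as over-50 patients and over-50 person-years for the period analysed, with expected events per arm. Over-50 counts can be drawn from the practice databases.
- Recompute with a two-sample formula on that basis and restate the power for two and for three years.
- Keep the 70,000 all-age list only as a recruitment guide, labelled as such, and stop describing N as study patients where it means list size.

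The cost is one recalculation and a rewritten paragraph. The stated power will be less favourable, mostly because of the two-sample formula and only in smaller part because of age.

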## Discussion

We have described the protocol of our trial of an electronic reminder system (the e-Nudge) that aims to change general practitioners' behaviour with respect to patients at risk of CVD. The trial will use routinely collected electronic data to repeatedly flag up high-risk patients and will measure the outcomes in terms of cardiovascular event rates and the risk profile of the over-50 year population. Electronic alert messages are now commonly used in the increasingly integrated software environment of UK primary care, but the evidence to support them is inconclusive. This trial will attempt to provide a more robust evidence base for the use of such tools for preventive care in UK general practice.

Operational issues that arose during the design of this project included those of data quality and software interoperability. Because the coding of clinical data under the nGMS is linked to remunerative targets, a widespread standardisation of Read coding has occurred since 2004 in areas of care related to chronic disease management. Without this development it is doubtful that a trial of this design could be conducted. Despite this, the use of alternative codes within the nGMS contract for data such as blood glucose values made the programming of the search algorithm challenging, particularly as more than one hospital laboratory (which generate these data for practices through electronic links) are involved in the study area. The identification of individual patients' smoking status was designed with current recording practice in mind, and this area of the program was the least secure in terms of accuracy, as it is not always possible to determine from electronic records exactly how long ago an ex-smoker quitted. Participating clinicians are made aware of the limitations of this part of the program so that adjustments can be made based on a knowledge of the patient's actual smoking history.

The e-Nudge Trial is an example of a new model of primary care research. It involves the flow of information out of the databases of participating practices to the practising teams, to then influence clinical behaviour and future data patterns. The search techniques involved include not only the identification of patients according to the presence in their notes of coded data, but a *computation *(using in this case the Framingham CVD algorithm) to define a more complex decision boundary between the high risk and low risk patients in a live database. This approach has become necessary in the light of the most recent guidelines on the prevention of cardiovascular disease [4], which explicitly support the definition of the hypertensive and hyperlipidaemic populations according to overall cardiovascular risk, estimated using both risk algorithms and other information known to the clinician. Such algorithms might lend themselves to future adaptation, by broadening the range of input risk variables, the use of alternative statistical models for the classification of high risk groups, and tailoring to regional populations [33].

The appendices describe the evidence behind the choices made in designing the study including thresholds, assumed values, and definitions.

### 1. Justification for the thresholds and search protocols used in the study

#### a) Age group

We decided to include in the searches only those patients over 50 yrs, as the prevalence of cardiovascular disease begins to climb steeply at this age [35]. As the main outcome involves a comparison of the effect of the intervention on event rates, this will avoid the dilution of each denominator population by low risk patients.

#### b) The high CVD risk group (Group 3)

The group at high risk of CVD (but who do not already have CHD, Stroke/TIA, or Diabetes) is defined not by a simple combination of diagnostic categories, but as the output of a risk prediction algorithm. The Framingham study data [39] is currently the best available source for patients without CVD under 75 years, and is recommended in the CHD NSF [3] and the 2004 British Hypertension Society Guidelines [40], despite some concern over its applicability to the UK population [41]. We will be using the *most recent values *as inputs for this algorithm. Whilst the recommended approach is to use values prior to treatment with antihypertensive or lipid lowering therapy, our approach is similar to that applied to individuals in existing prediction tools [42,43] that can compare "pre-treatment" with "post-treatment" risk, to emphasise the impact on risk of intervention such as drug therapy and lifestyle modification. We are therefore making no distinction between the estimated risk levels of two patients with identical risk profiles including blood pressure, one of whom is on antihypertensive treatment and the other is not. In fact the treated patient, whilst having a significantly lower cardiovascular risk than before commencing therapy, still has a higher risk (not recognised by our search protocol) than the otherwise similar patient with the same blood pressure not requiring therapy. Despite this limitation, this approach is currently the most effective means of utilising primary care data (where "pre-treatment" blood pressure or lipid levels are often not identifiable), and is very much in keeping with the monitoring process of the QOF, which measures performance according to the most recent values of variables such as blood pressure or serum cholesterol.

### 2. Identifying patients with undiagnosed diabetes

The application of these searches provides an opportunity to identify patients who may have undiagnosed diabetes. Such searches have been shown to include patients absent from diabetes registers with blood glucose measurements above the usual diagnostic threshold of 11.1 mmol/L. For instance, the Diabetes Audit and Research in Tayside Scotland (DARTS) study [44] identified 701 patients with isolated hyperglycaemia in a number of primary and secondary care registers, from a population of 391 274. This figure was 9.2% of the 7596 identified with diabetes. Whilst such patients (particularly if asymptomatic) require further investigation to clarify their diabetes status [45], a number may benefit through earlier detection and treatment if diabetes is confirmed. During pilot work in one local practice, a search identified the following (see Table 2):

**Table 2 T2:** 

Currently registered patients:	12,245
Plasma glucose on record ≥ 11.1 mmol/L but no diagnosis of diabetes	6

Of these six:

1. Four patients had undiagnosed type 2 diabetes later confirmed by fasting blood glucose measurements.

2. One patient had impaired fasting glycaemia (FBG 6.9 mmol/L) and is awaiting further investigation with OGTT to exclude diabetes.

3. One patient had probable steroid induced hyperglycaemia and has had a normal blood glucose value recorded since stopping the steroids.

We are therefore including as part of the regular searches a query to identify such patients, who may have undiagnosed diabetes based on previous raised measurements. Such patients identified in this study will need to have a subsequent non-diabetic fasting blood glucose level (≤6.9 mmol/L) or Oral Glucose Tolerance Test in order that future searches classify them as not having diabetes (see also appendix 5 below). Some of these patients in whom diabetes appears to be refuted by fasting measurements may go on to have further abnormal plasma glucose levels, in which case they will again be identified as possible cases (Group 5) until a further normal fasting glucose level is obtained, or a diagnosis of diabetes is made.

### 3. Screening for type 2 diabetes in populations at risk of CVD

Diabetes UK has issued a position statement on the early identification of people with type 2 diabetes [46]. Among other groups, this document identifies people with ischaemic heart disease, cerebrovascular disease, peripheral vascular disease or hypertension as high risk groups justifying screening, with a screening interval of three years. However a reliable and practical screening test has not been established. Whilst fasting plasma glucose estimation is significantly more specific than random plasma glucose estimation, it is less practical. In addition to the detection of possibly undiagnosed patients described above, we have therefore designed the study to encourage blood glucose testing at least every three years in groups who either have, or who are at high risk of CVD. These tests can be carried out during the routine blood checks that patients receive for monitoring of lipid lowering or anti-hypertensive therapies. Therefore negative diabetes status will only be assumed if the patient is not on the Diabetes register *and *a normal plasma glucose level (random or fasting) is present in the record within the three years prior to the search. We will be allowing the follow up of patients with borderline plasma glucose levels to remain at the discretion of the practices. (The recently published Joint British Societies guidelines on prevention of cardiovascular disease in clinical practice (JBS 2), clarifies currently recommended practice in this area for the first time [4].) This study may be able to determine whether this approach is useful as a means of detecting type 2 diabetes earlier in these groups, given its practicality and low cost. Practices are at liberty to use more specific screening tests on any individual whom they feel justifies it.

### 4. Search groups 1, 3 and 4

The Group 1 patients are identified on the basis of thresholds used as audit targets in the nGMS contract for secondary prevention. Whilst these treatment targets are essentially arbitrary [47], they have been selected through extensive discussions between the Department of Health and expert advisory bodies. Following advice in the National Service Framework for Diabetes [48] and supported by the 2004 BHS guidelines [40] and JBS 2 [4], the nGMS QOF recommends that patients with diabetes are treated as if they already have cardiovascular disease in terms of cholesterol and blood pressure control. The latter in fact requires tighter target levels than for patients with CVD alone. For this reason they will similarly be regarded as secondary prevention patients in this study.

For primary prevention (Group 3 and Group 4), the British Hypertension Society Guidelines (2004) recommend a 10-year risk of developing cardiovascular disease of ≥20% as a threshold for treatment of grade I hypertension with antihypertensive drugs, or lipid lowering therapy in all groups at this risk level up to the age of 80 yrs [40]. However, the Framingham algorithm is not designed to be used in patients over 75 years of age, and the CHD NSF [3] recommends that the systematic identification of new primary prevention candidates (particularly for lipid lowering therapy) should stop at age 74 years. However, older hypertensive patients benefit from blood pressure reduction and the identification of patients with grade II hypertension or higher, based on serially elevated blood pressure measurements can therefore be justified above this age limit. Whilst it might be justifiable to reduce this threshold (for instance to identify older patients with grade I rather than grade II hypertension), this would involve identifying potentially large numbers of patients whose need for treatment was not as clear, adding considerably to the workload involved.

